### Adverse events and severe adverse events

2.9

#### Adverse events: fractures associated with rehabilitation exercise

2.9.1

Severe adverse events: persistent or severe disability or dysfunction caused by rehabilitation exercise.

If adverse or severe adverse events occur, the relationship between them and the intervention will be assessed, the intensity and mode of intervention will be adjusted, the intervention will be suspended if necessary, and the participants will receive appropriate treatment. We will immediately provide a diagnosis and treatment and report the occurrence in a timely manner while compensating the participant according to the relevant laws and regulations of our country.

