#### Outline

2.5.1

In this study, 320 elderly participants ≥70 years old will be randomly divided into the intervention group and control group. The intervention group will be given a routine diagnosis and treatment, a CGA and multi-disciplinary management for 12 months, and the control group will be followed up for 12 months with routine management for basic diseases. A flowchart of the trial is shown in Figure 1.

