### Intervention

2.6

Participants in the intervention group will receive a CGA and receive 12 months multi-disciplinary management. Interventions will be carried out by a multi-disciplinary team (including physicians, nurses, nutritionists, rehabilitation physicians, pharmacists, TCM physicians). A brief CGA will be carried out by nurses during the three days of hospitalization, including evaluations of the following data: hearing impairment, visual impairment, masticatory disorder, risk of fall and imbalance, history of falls, urinary incontinence and fecal incontinence, chronic constipation, and chronic pain. The specialized CGA and interventions are as follows:

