1.Nutrition aspectAssessment: Age, grip strength, daily physical activity, NRS-2002 score, clinical diagnosis (especially sarcopenia), laboratory results, human body composition analysis (Inbody 720), dietary survey.Advice: A reasonable dietary plan will be formulated by the nutritionist.2.RehabilitationAssessment: SPPB, physical fitness tests,^[46]^ including a 30-second sit-to-stand test^[47–49]^ to assess lower body strength, a 30-second arm curl test^[50]^ to assess upper body strength, a 2-minutes step test^[51]^ to assess the cardiopulmonary function and aerobic endurance, a chair sit-and-reach test^[52,53]^ to assess lower body flexibility, a back scratch test^[54]^ to assess upper body flexibility, and a time-up-and-go test (TUG)^[53,54]^ to evaluate dynamic balance and agility.Advice: A set of rehabilitation exercises will be taught, including breath adjustment, posture adjustment, guidance for contracting abdominal muscles and pelvic floor muscles, head and neck stretching, back scratching, sitting forward stretching, sitting elastic belt assisted upper limb movement, heel lifting and stepping. Each participant will be given a sports manual with exercise instructions and safety information. During the period of hospitalization, all training sessions will be carefully supervised by a rehabilitation physician experienced in therapeutic training. Participants will perform 3 to 20 repetitions for each exercise and 3 to 5 times per week for 12 months, and accurately record the frequency, time and feelings concerning exercise each week, gradually increasing to the maximum tolerance and safety intensity. Participants will also be encouraged to exercise on their own and walk for a few minutes each day.3.Multi-drug evaluationAssessment: Medication appropriateness index (MAI),^[55]^ review of the type, measurement and quantity of drugs used by patients during hospitalization.Advice: Pharmacists will participate in the administration of drugs to the participants, potentially harmful drugs or doses will be revised and patients will receive instructions concerning medication when discharged.4.TCMAssessment: TCM physicians will comprehensively and systematically assess the participants based on the TCM theory of syndrome differentiation, including a TCM tongue diagnosis and pulse diagnosis.Advice: TCM physicians will deliver guidance on performing acupoint massage related to constipation and insomnia, including Zhigou, Zusanli, Dachangshu, Neiguan, Shenmen, and Sanyinchiao. Each participant will be instructed on 0 to 4 related acupoints, and each acupoint will be massaged for 5 minutes every day.5.Patient educationNurses will issue a patient education manual to each participant, covering the basic introduction of frailty, fall prevention education, first-aid knowledge and cardiovascular medicine guidance. All participants in both groups will undergo routine management.

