Statistical analyses: We will conduct an intention-to-treat (ITT) analysis for the primary analysis, including primary and secondary outcomes, with a per-protocol (PP) analysis used for the sensitivity analysis. The ITT population is defined as all randomized participants in the study, and the PP population is defined as all randomized participants who were actually compliant with their treatment. The participants clinical features will be compared between the intervention and control groups. Continuous variables will be expressed as the mean ± standard deviation in a normal distribution and median and interquartile range in a non-normal distribution, and categorical variables will be expressed as numbers and percentages. Baseline characteristics will be compared by χ^2^ tests or Fishers exact tests for categorical variables and *t*-tests or Wilcoxons rank sum tests for continuous variables. A covariance analysis will be used to analyze the Fried phenotype, SPPB and modified means of the 2 groups, taking the central effect of the test into account, and the 95% confidence interval (CI) of the difference between the 2 groups will be calculated. Only when the above 2 main indicators satisfy the statistical hypothesis (superior effect), can the hypothesis be considered valid. For time-event data, the Kaplan–Meier method will be used to estimate death, non-elective hospital readmission and fall events. A log rank test will be performed for the 2 groups. A Cox proportional-hazard regression model will be used to calculate the effect of potential risk factors on the events. We will summarize the number of enrollments and completion of each center, list the drop-outs, compare the total drop-out rate and list the reasons for termination in detail and compare the characteristics between those with missing outcome data and those who have completed follow-up. The safety evaluation table will be included to describe the number of adverse events and the incidence of adverse events, serious adverse events, adverse reactions and serious adverse reactions in the two groups. Statistical significance will be set at a 2-sided *P* value <.05.

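### Adverse events are defined as harms of rehabilitation exercise, which as a study component only the intervention arm receives, so the adverse event rows of the two-group safety table are not comparable between arms

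*Protocol article*

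**What the plan says.** The only definitions are in section 2.9.1 of the protocol article. The heading reads "Adverse events: fractures associated with rehabilitation exercise", and the line below it reads "Severe adverse events: persistent or severe disability or dysfunction caused by rehabilitation exercise". The same section adds that once an event occurs, "the relationship between them and the intervention will be assessed".

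Section 2.8 plans a safety table giving the number and incidence of "adverse events, serious adverse events, adverse reactions and serious adverse reactions in the two groups". The table is descriptive, and no test is named for it.

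On who receives the exercise, section 2.6 says "Participants in the intervention group will receive a CGA and receive 12 months multi-disciplinary management", and the rehabilitation exercises are one part of that management. Under section 2.5.1, "the control group will be followed up for 12 months with routine management for basic diseases". The other parts are a diet plan, a pharmacist's review in which "potentially harmful drugs or doses will be revised", acupoint massage and patient education.

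Table 1 schedules adverse event recording at all four visits. Section 2.7 plans telephone reviews about two to three times a month for all participants.

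**The concern.** A between-arm safety table is informative only if the same thing can be counted in both columns. Here attribution to one treatment component is part of the event itself, and only one arm is given that component by the study. Two patients with the same hip fracture could be recorded differently: one as an adverse event because the patient was on the programme, the other as nothing.

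Two errors of interpretation could follow. A count in the intervention arm beside an empty control column may be read as excess harm when total injuries are equal or even lower. Conversely, a short list of exercise fractures may be read as a clean safety record when harms from changed medication, diet or massage, and lesser exercise injuries, had no row to go in. The population is frail inpatients aged 70 or over, and the Discussion itself says that the safety of exercise or diet still needs large randomised studies.

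**Working it through.** **1. The passages side by side.**

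| Place | What it requires |
|---|---|
| 2.9.1, definitions | The event must be associated with, or caused by, rehabilitation exercise |
| 2.9.1, handling | The relationship to the intervention is judged after the event |
| 2.8, safety table | Events and reactions are shown as separate rows, in both groups |
| 2.6 and 2.5.1 | The exercise programme is in the intervention arm; control has routine management |
| Table 1 | Adverse events are recorded at all four visits |

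Rows one and two conflict: a relationship that is part of the definition leaves little to assess later. Rows one and three conflict: a reaction is ordinarily an event judged to be related, so if every event is already exercise-related, the event and reaction rows hold the same cases. Rows one and four together make the control count zero or near zero. The wording also differs: 2.9.1 defines severe events, while 2.8 tabulates serious ones.

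**2. How the table behaves when control is empty.** The protocol gives no adverse event rate, safety power or safety sample size, so there is no figure to reproduce. What follows is illustration. Inputs from the documents: 160 per arm (2.5.3), 15% attrition (2.4), so 160 × 0.85 = 136 per arm, and a two-sided 0.05 level (2.8).

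With k events in the intervention arm and 0 in control, and equal arms of n, the two-sided Fisher p is 2 × C(n, k) / C(2n, k).

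- n = 160, k = 5: p = 0.061
- n = 160, k = 6: p = 0.030
- n = 136, k = 6: p = 0.030

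The probability of 6 or more events is the binomial tail P(X ≥ 6) for an assumed true rate of exercise-attributed events (none of these rates is in the documents):

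| Assumed rate | 160 per arm | 136 per arm |
|---|---|---|
| 2% | 0.10 | 0.06 |
| 3% | 0.35 | 0.23 |
| 5% | 0.82 | 0.68 |
| 8% | 0.99 | 0.97 |

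So the rows can show exercise harm in the intervention arm. They would do so whatever the all-cause picture. Suppose each arm had 8 fractures and 6 of those in the intervention arm were attributed to exercise: the table would read 6 against 0, although the true comparison is 8 against 8.

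**3. The same table under a cause-neutral definition.** Power by the usual normal approximation is Φ[(|p1 − p2| − 1.96·√(2p̄(1 − p̄)/n)) / √((p1(1 − p1) + p2(1 − p2))/n)], where p̄ is the mean of p1 and p2. The rates are again assumed.

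| Control | Intervention | 160 per arm | 136 per arm |
|---|---|---|---|
| 10% | 20% | 0.71 | 0.64 |
| 20% | 10% | 0.71 | 0.64 |
| 10% | 15% | 0.27 | 0.24 |
| 10% | 5% | 0.40 | 0.35 |

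Power is modest for small differences, but the comparison can now move in both directions.

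**4. What lies outside the definition.** Harm from drug or dose changes, from the diet plan and from acupoint massage; exercise injuries that are neither a fracture nor lasting or severe loss of function; and any injury in control not linked to rehabilitation exercise.

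**The case against.** The strongest case on the other side has four parts.

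*Harm is measured elsewhere.* Sections 2.1 and 2.8 compare death, non-elective readmission and falls between groups by Kaplan–Meier and log-rank, with no causation condition. BADL, CFS and NRS-2002 are also secondary outcomes. This stands, and it means a reader should not infer that the trial could support no safety conclusion. It does not close the gap: fractures without a fall, lesser exercise injuries, and drug or diet harms that lead to neither readmission nor death still have no place as events, though functional or nutritional decline may register on the scales.

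*The table can detect something.* A reader might infer that it cannot detect harm in either direction. That is too strong, as step 2 shows: exercise harm in the intervention arm would appear.

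*Control need not be exactly zero.* The definition says rehabilitation exercise, not study exercise. Eligibility excludes regular moderate exercise or rehabilitation-facility treatment in the past three months, and expected residence in a rehabilitation centre in the coming year. It does not bar control patients from exercising or having rehabilitation in routine care. This stands, so zero or near zero is the supportable wording. It is also true that the table is descriptive.

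*The lines may only list expected events.* The unrestricted row in Table 1, the event and reaction split and the later causality step all suggest that wider recording was intended, and the article condenses a longer protocol. That may be so, but the article contains no wider definition. What it does state is restrictive and at odds with those three places.

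**Conclusion.** The concern holds in a limited form. The stated definitions capture only exercise-attributed harm, so the adverse event rows are lopsided by construction, cannot show an excess of events in control or a net reduction, and miss harm from the other active components. They also contradict the event and reaction split in 2.8 and the causality step in 2.9.1. This is a rule stated wrongly, not a detail left to another document.

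Its size cannot be given as a bias in a stated figure, because no adverse event rate is given. The illustration (6 against 0 giving p = 0.030) rests on control staying at zero and on assumed event rates, and no such test is planned. The conclusion assumes that site staff apply 2.9.1 as written. The primary outcomes and their analysis are unaffected, and the comparisons of death, readmission and falls remain valid sources of safety information.

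**What to change.** Reconcile 2.9.1 with 2.8 and Table 1:

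- Use one definition in both arms: any untoward medical occurrence after randomisation, whatever its cause.
- Define seriousness by outcome (death, threat to life, hospital admission or its prolongation, persistent disability), and use one term, serious, throughout.
- Record relatedness as a separate item for each intervention component. Events judged related then form the adverse reaction rows.
- Ask the same questions in the same way in both arms, at the scheduled visits and in the telephone reviews.
- Keep exercise-related fracture and disability as events of special interest, reported alongside the all-cause rows.

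The cost is revised protocol and case report form wording and more events to record; no new visits or calls are needed. Recruitment was under way when the article was written, and events not recorded at the time are hard to recover reliably. The change should therefore be made early and applied to both arms from the same date.

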#### Ethics and dissemination

2.9.2

This study was reviewed and approved by Ethics Committee of Beijing Hospital, China. (ID number: 2019BJYYEC-045–02). All participants will sign their informed consent according to the Declaration of Helsinki prior to data collection. The results of this trial will be presented at scientific conferences and published in peer-reviewed journals. The design and development of this study is patient-centered. Patients were not involved in the development or design of the study. The burden of the intervention will not be assessed by patients themselves. Patients or their guardians will receive a verbal and written summary of the tests and evaluation results, as well as the study results that are allowed to be disseminated to them.

## Discussion

3

At present, there is still a lack of effective guidelines for the management of elderly frailty patients. As the most effective measure to improve physical fitness and muscle strength, rehabilitation exercise and reasonable diet have great heterogeneity. Moreover, the safety, cost-effectiveness, long-term sustainability and population acceptance ability of rehabilitation exercise or reasonable diet still need large randomized control tests or systematic reviews to verify. As a large nation of catering, the food culture of China is very pluralistic, but many old people in China have a deep-rooted food culture. Simple nutritional assessment and diet are particularly needed to guide the daily diet of the elderly. We hope that the nutrition intervention program designed in our study can be popularized. In addition, we will teach the appropriate content of standard rehabilitation exercise according to the results of physical fitness assessment, and recommend the best exercise intensity to the patients. Moreover, standardized medication guidance, simple acupoint massage on insomnia and constipation and patient education can be well performed by a team in clinical work. A remarkable characteristic of our study is the utilization of an interdisciplinary team (physicians, nurses, nutritionists, rehabilitation physicians, pharmacists, TCM physicians) that manages for inpatients in different clinical departments. Our result may be able to show that an individualized multi-component prescription for elderly frailty patients is plausible.

This paper outlines the protocol for a randomized, single-blind, parallel, multi-center clinical study to explore the prognosis of elderly frailty patients after CGA and multi-disciplinary management in China. The main purpose of this paper is to explore a diagnosis and treatment management mode for elderly frailty patients, rather than to evaluate the weight of a specific measure among a variety of interventions, since the effect of each measure has been clearly demonstrated in previous studies. If our hypotheses are correct, we can establish a set of systematic and standardized management mode. Compared with the control group, the cost-effectiveness analysis of CGA and multi-disciplinary management is the focus of our research, and also the key part of whether the research results can be popularized.

The main limitation to our study is that it takes a little long time to evaluate the particularly frailty elderly patients, but only an accurate CGA can better complete the intervention measures, and we can cooperate with all patients to complete the evaluation content when they are enrolled through strict inclusion-exclusion criteria and the assessment can also be conducted in several times, and for simple questions, we can also consult the patients family members or caregivers.

There is strong evidence to support CGA in a hospital setting in the Europe and North America, and randomized evidence from China would further strengthen the evidence base. The intervention being tested is CGA with the addition of TCM, if it is effective, it may further supplement the existing CGA. The study results will be extremely relevant to elderly patients. This protocol, if beneficial, will demonstrate the interaction of various intervention strategies, wherein a rehabilitation exercise, diet adjustment, multi-drug evaluation, acupoint massage in TCM and patient education are included, will help improve elderly frailty patients, and will be useful for clinicians, nurses, policymakers, public health authorities and the general population.

### Trial status

3.1

At present, hospital and patient recruitment for this trial is ongoing. The first patient was included in June 2019 and recruitment is expected to be completed in December 2020. Protocol version number is 1.0, dated March 10, 2019.
